**Figure 1 F1:**
[figure not shown]
Study design of Study Part 1.

Demographic information, including age, gender, nationality, and current employment situation, are asked at enrolment. The participants are also asked to provide contact details for follow-up measurement occasions. Post measurement (t_2_) comprises also information about the rehabilitation program and health indicators for subgroup-analyses. Information regarding the employment status and disability pension are reported to the research team of the Karlsruhe Institute of Technology (KIT) via the Deutsche Rentenversicherung (DRV) Knappschaft-Bahn-See during the last year of follow-up, if participants gave their consent at t_0_ or t_1_. All other instruments described below are used at the baseline measurement (t_0_), the pre and post measurements (t_1_, t_2_), and the follow-up measurements (t_3_–t_8_).

##### Health-related quality of life

2.1.3.1

A commonly used measure of health-related quality of life is the World Health Organization Quality-of-Life Scale (WHOQOL-BREF) questionnaire developed by the World Health Organization (23). This questionnaire contains 26 items with the dimensions physical health, mental health, social relationships and environment. In this study the scales physical health and mental health with a total of 13 items are used. A large-scale study conducted in 23 countries showed good reliability for the physical health (*α* = 0.82) and mental health (*α* = 0.81) scales (24). The study also supported the construct validity of the questionnaire.

##### Work ability

2.1.3.2

The Work Ability Index (WAI) is an internationally established instrument for measuring work ability (25). The short version consists of ten questions covering seven dimensions: (1) current work ability compared to the best ever, (2) current work ability compared to the demands of the job, (3) number of current illnesses diagnosed by a doctor, (4) estimated impairment of work performance due to illness, (5) days of sick leave in the last 12 months, (6) assessment of one's own work ability in two years, and (7) mental performance reserves. The result is a total score between 7 and a maximum of 49, which indicates the assessed ability to cope with existing work demands (25). The reliability of the WAI can be considered satisfactory with a Cronbach's alpha of 0.78. With regard to the validity of the questionnaire, the WAI has been shown to be able to predict early retirement and the duration of long-term disability (26, 27).

##### Weight status

2.1.3.3

The Body Mass Index (BMI) is a widely used measure of overweight and obesity. According to a classification provided by the World Health Organization (WHO), a person is considered overweight with a BMI of 25–30 kg/m^2^ and obese with a BMI of ≥30 kg/m^2^. Obesity is also classified according to severity (28). Thus, adults with a BMI of 30–34.9 kg/m^2^ are classified as severity I, adults with a BMI of 35–39.9 kg/m^2^ as severity II, and adults with a BMI of ≥40 kg/m^2^ as severity III. The BMI is considered an appropriate measure of overweight alongside other measures such as waist circumference or waist-hip ratio (29, 30). Participants are asked to provide information about their body weight in kilograms and height in meters.

##### Physical activity

2.1.3.4

The items of the Patient-Centered Assessment and Counselling for Exercise Plus Nutrition (PACE+), which were originally developed for adolescents (31), are used to assess physical activity in everyday life. The items were translated into German (32) and successfully used in comprehensive long-term studies not only with children and adolescents, but also with adults (33, 34). Two items record how many days per week participants were active for at least 60 min at moderate intensity. The first item refers to the last week and the second to a normal week. The response scale ranges from 0 to 7 days. Before answering these questions, physical activity is defined as any activity that makes the heart beat faster and increases breathing for some time. Examples such as walking to work, running, dancing, and swimming are given. The average of the two items builds the final physical activity score. The items showed interclass correlation coefficients between 0.64 and 0.79, which can be considered good. Validity can also be rated as good, as data from the PACE + items correlated significantly with accelerometer data [*r* = 0.40, *p* < .001, (31)]. A study using the German formulation of the items showed comparable values in terms of test retest reliability (*r* = 0.68, *p* < 0.05) and validity (*r* = 0.29 with accelerometer data, *p* < 0.05) (33).

##### Employment status

2.1.3.5

Employment status of the participants are provided by the pension fund once a year during follow-up (three measurement occasions in total), if the participants gave their consent at t_0_ or t_1_. The data reflect, the number of days the participants were employed between the measurement occasions. If participants were not employed, information are provided on the payment of compensation for these periods (e.g., unemployment benefit, disability pension, care support allowance).

#### Data analysis

2.1.4

Data will be analyzed by the KIT research team. Questionnaire data are pseudonymized through personal codes and contact details are stored separately from questionnaire data. The identification of participants is possible only through a password-protected, locally stored file by the research team. A research assistant independently checks the accuracy of the data entry. Missing data will be analyzed to what extent they are systematic and, if necessary, treated with multiple imputation or the full-information maximum likelihood approach.

In order to ensure comprehensive analysis and interpretation of the data collected in our study, a multi-faceted statistical approach will be employed. Initially, repeated measures analyses of variance will be utilized to assess changes in subjective health, work ability, BMI, and physical activity behavior over time. This method is particularly effective for analyzing data where multiple measurements are recorded for the same subjects. Analysis of variance with repeated measurement allows for the evaluation of both within-subjects effects (changes over time) and between-subjects effects (differences among groups). In addition, latent growth curve modeling (LGCM) will be implemented to explore the trajectories of the aforementioned parameters across the study period. LGCM provides a flexible framework to model nonlinear growth trajectories, accommodating various shapes of developmental change (35). This is particularly pertinent for our study, as it enables the examination of individual differences in change patterns, thereby offering a deeper understanding of how rehabilitation programs impact individuals over time. Age, gender, the duration and the completement of the rehabilitation program will be included as control variables.

### Methods of Study Part 2

2.2

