A power analysis was conducted with a small effect size as the evidence regarding the efficacy of rehabilitation programs is insufficient. A meta-analysis about the effects of cardio-vascular rehabilitation on health-related quality of life yielded effect sizes of 0.17–0.25 (21). Due to a large heterogeneity in this meta-analysis and because cardio-vascular rehabilitation programs are different from orthopedic rehabilitation programs, a standard mean effect size of 0.10 was chosen. The power analysis with Cohens *f* = 0.05, *α *= 0.05, 1-*β* = 0.80, a correlation among repeated measures of *r* = 0.50 and a design with eight measurement occasions since the start of rehabilitation program using an analysis of variance (ANOVA) with repeated measurements (within-between interaction) resulted in *n* = 360 participants. Considering a dropout after each measurement occasion of 15%, the recruitment of *n* = 1,101 participants is planned.

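### Multiple imputation or FIML depends on a check for systematic missingness that cannot justify omitting it, although the plan's own dropout rate leaves about 68% of participants incomplete over t1 to t8

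*Protocol article*

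**What the plan says.** The rule is in the Data analysis section of Study Part 1 (2.1.4): "Missing data will be analyzed to what extent they are systematic and, if necessary, treated with multiple imputation or the full-information maximum likelihood approach". The text does not define when treatment becomes necessary, and it does not say how incomplete records are handled otherwise.

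The same section then names the analyses. The first is "Initially, repeated measures analyses of variance will be utilized to assess changes in subjective health, work ability, BMI, and physical activity behavior over time". The second is "In addition, latent growth curve modeling (LGCM) will be implemented to explore the trajectories of the aforementioned parameters across the study period". Neither is labelled primary.

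Section 2.1.1 (Sampling and participants) bases the power analysis on "a design with eight measurement occasions since the start of rehabilitation program", using a repeated-measures ANOVA with a within-between interaction. This gives 360 participants. It continues: "Considering a dropout after each measurement occasion of 15%, the recruitment of" 1,101 participants is planned. The Discussion accepts that long follow-up with many occasions often brings high attrition, and offers reminders as the countermeasure.

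**The concern.** The condition decides whether incomplete records are used at all, and it rests on a diagnostic that cannot carry that decision. A check on observed data may reveal that dropout is related to earlier answers. It cannot show that dropout is unrelated to the answers that were never given. A negative result is therefore no licence for deletion.

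Durability over three years is a stated aim of Study Part 1, and most participants are expected to be incomplete by the last occasion. If a classical ANOVA were run on those with all occasions, the long-term estimates would describe the patients who kept responding. They may differ from those who stopped, in a direction that cannot be known in advance. The early contrasts would also lose information already collected.

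**Working it through.** **Inputs.** All are from section 2.1.1: Cohen's f = 0.05, alpha = 0.05, power = 0.80, correlation r = 0.50, eight occasions (t1 to t8), n = 360, dropout 15% after each occasion, recruitment 1,101. The number of groups in the interaction is not stated; two is assumed.

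**1. Reproduce the 360.** For the within-between interaction, lambda = f² × N × m / (1 − r) = 0.0025 × 360 × 8 / 0.5 = 14.4, with df1 = (2 − 1)(8 − 1) = 7 and df2 = (360 − 2) × 7 = 2,506. The smallest N with power of at least 0.80 is 360, as stated.

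**2. Reproduce the 1,101.** There are seven intervals from t1 to t8. Dividing gives 360 / 0.85^7 = 1,123, which is 2% above the stated figure. Multiplying gives 360 × 1.15^8 = 1,101.2, which matches it. On either route the aim is roughly 360 participants remaining at the end. The small gap is not a point of this review.

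**3. Expected completeness.** Apply 15% loss at each step to 1,101 recruits, assuming that dropout is permanent:

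| Occasion | Still observed | Cumulative loss |
|---|---|---|
| t1 | 1,101 | 0% |
| t2 | 936 | 15.0% |
| t3 | 795 | 27.8% |
| t4 | 676 | 38.6% |
| t5 | 575 | 47.8% |
| t6 | 489 | 55.6% |
| t7 | 415 | 62.3% |
| t8 | 353 | 67.9% |

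So 0.85^7 = 0.321: 353 are complete and about 748 are not. Skipped questionnaires followed by a return would raise the incomplete share further.

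**4. What an eight-occasion completer set would discard.** The table sums to 5,340 expected questionnaires. Completers supply 353 × 8 = 2,824. The other 2,516 (2,516 / 5,340 = 47%) would go unused.

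**5. Worst case for the pre-post contrast.** Section 2.1.3 names t1 and t2 as the measurements that assess effectivity. All available pairs: 1,101 × 0.85 = 936. Pairs among t8 completers: 353. The standard error is proportional to 1/√n, so the ratio is √(936 / 353) = 1.63, or 63% larger; 936 − 353 = 583 pairs would be set aside.

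**6. The two branches of the rule.** If the check finds systematic missingness, imputation or FIML follows. If it does not, nothing is specified. Even when dropout really is completely at random, deletion costs the information in steps 4 and 5. When dropout depends on unobserved outcomes, the check may miss it. Neither case is a reason to withhold a method that uses all records.

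**The case against.** Several parts of the opposing case stand.

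- **Complete-case analysis is not stated.** It is an inference from the form of a classical repeated-measures ANOVA and the silence about the negative branch. With two thirds expected to be incomplete, the authors might well judge treatment necessary. That reply is fair, but the text ties the decision to whether missingness is systematic and gives no threshold for its amount.
- **The sample size does not settle the analysis.** A reader might take the inflation from 360 to 1,101 as proof of a completer analysis. Inflating for dropout is ordinary conservative planning, and Study Part 2 is sized with an ANOVA but analysed with multilevel models. The sizing is used here only for the expected extent of dropout.
- **A suitable model is already planned.** The growth curve model covers the same outcomes and can use FIML. This narrows the point, but the article makes FIML subject to the same condition.
- **A large power loss might be inferred.** For a paired change of 0.10 SD at r = 0.50, power would be about 86% with 936 pairs and 47% with 353. The documents do not restrict the t1-t2 comparison to t8 completers, and a two-occasion analysis would keep all pairs. The planned eight-occasion test already allows for the loss.
- **Loss of everyone recruited at t1 might be inferred,** because they have no t0. The ANOVA used for sizing starts at t1, so this does not follow.
- **Bias in favour of rehabilitation might be inferred.** It is plausible, but nothing in the document fixes the direction. FIML and multiple imputation, as ordinarily used, also rest on missingness at random.

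Details of sensitivity analyses and auxiliary variables commonly belong in an analysis plan that is not shown, so their absence is not criticised.

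**Conclusion.** The concern holds as a badly fixed rule, not as a demonstrated completer analysis. Use of imputation or FIML is conditional on a test that cannot support the negative decision, and the negative branch is empty. The size follows from the protocol's own planning rate: about 68% incomplete over t1 to t8, and 353 of 1,101 complete. The consequences are a risk of selection bias of unknown direction in the three-year estimates and loss of precision. The 63% larger standard error for t1-t2 is an upper, worst-case figure.

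These figures assume that the 15% rate is realised, that dropout is permanent, and that a negative check would lead to a classical ANOVA on complete records.

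**What to change.** Delete the condition in section 2.1.4. State that the main analysis is a likelihood-based mixed model, or the already planned growth curve model with FIML, on all participants with at least one measurement, whatever a check of missingness shows. Keep repeated-measures ANOVA as a secondary analysis. The description of missingness patterns can stay as reporting, without deciding the method.

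Because this relies on missingness at random, add a simple sensitivity analysis that assumes worse outcomes after dropout. Pension-fund employment data can serve as auxiliary variables where consent and availability allow. Section 2.1.3.5 says "Employment status of the participants are provided by the pension fund once a year during follow-up (three measurement occasions in total"), subject to consent, but the article does not say that delivery continues for people who stop answering, so this should be confirmed first.

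The cost is a change of wording and a little analysis work. No new data are needed, and neither 360 nor 1,101 changes.

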## Background

1

Rehabilitation services are a vital and integral component of the German health care system, especially in the context of orthopedic impairments. These services not only constitute a significant financial investment within the system (1, 2) but also play a crucial role in enabling individuals with health impairments to return to work and regain quality of life. On the one hand, patients are supported in their healing process by health professionals, aiming to enhance their overall health and work ability as they progress through the program. On the other hand, patients are educated and guided to adopt health-promoting behaviors, such as regular physical activity, to promote long-term health. This dual focus ensures that patients not only recover but also acquire the necessary skills and understanding to maintain their health in the long-term, reducing the likelihood of requiring further rehabilitation services. By targeting these areas, rehabilitation programs are designed to provide comprehensive care that addresses both the immediate needs and future well-being of patients with orthopedic impairments.

Studies on cardiovascular (3), oncological (4), neurological (5) and musculoskeletal (6, 7) rehabilitation interventions showed positive effects on previously impaired health parameters. In addition, a reduced mortality rate was observed (3, 8). A recent meta-analysis yielded that orthopedic rehabilitation programs in Germany increase patients' quality of life and work ability (9). However, the existing research on the effectiveness of rehabilitation programs reveals some critical gaps and shortcomings that warrant further investigation. Most notably, a control group is an essential component for robustly evaluating the effectivity of the intervention which is missing in many studies. Moreover, the durability of these positive effects remains largely unclear, with few studies incorporating a follow-up period exceeding 12 months (9). This research gap regarding long-term durability underscores the need for more comprehensive research to optimize the effectivity of rehabilitation programs.

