#### Sampling and participants

2.1.1

Eligibility criteria for participating in the study are that patients need to be at least 18 years old, have basic knowledge of the German language, and the reason for their rehabilitation is an orthopedic impairment prescribed by the German pension fund. There are no further inclusion criteria regarding the type of orthopedic impairment. Participants will be recruited at two different measurement occasions, one before the rehabilitation program starts and one during the first few days of the rehabilitation program. For the first measurement occasion, patients receive information about the study and the first questionnaire via post several weeks before the rehabilitation program starts (t_0_). Rehabilitation centers send out the study material together with the usual information material regarding the rehabilitation program itself. Patients that did not participate in the study at the first measurement occasion can still be recruited at the second measurement occasion (t_1_) which is taking place at the beginning of the rehabilitation program in the rehabilitation centers. Participants that already participated in the first measurement occasion (before rehabilitation started) also fill out the second questionnaire at the beginning of the rehabilitation program (t_1_). This procedure allows for a comparison of the indicators' development from the time without a rehabilitation program with the indicators' development after the rehabilitation program has started. Participants will be informed of the purpose of the study and will give their written consent to participate voluntarily. Currently, five rehabilitation centers in Germany are part of the study. The patients will receive a 50€ voucher, if they fill out the questionnaires at all measurement occasions. Participants are reminded by the research team via e-Mail or phone to fill out the questionnaires to increase participation in the study.

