#### Rehabilitation programs

2.1.2

Orthopedic rehabilitations programs in Germany are offered stationary or as an outpatient program in rehabilitation centers. Typically, rehabilitation programs last three to four weeks and comprise different services such as physiotherapy, medical training therapy, and health education. For some indications, standards for treatments exist based on scientific evidence such as for knee and hip joints, but this is not the case for all orthopedic indications (22). Therefore, the content and structure of rehabilitation programs can vary between rehabilitation centers. Rehabilitation programs at the participating rehabilitation centers will be executed as usual and the impact of the study will be limited to the data collection. Therefore, this treatment is not an intervention provided by the research team, but rather treatment as usual.

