## Discussion

3

The aims of this study are (1) to evaluate the effectiveness and the durability of effects of orthopedic rehabilitation programs and (2) to gather a deeper understanding of how psychological determinants influence aftercare health behaviors.

Study Part 1 includes a three-year follow-up period after rehabilitation, which is much longer than most previous studies (9) and enables the evaluation of long-term effects. Additionally, a control period without treatment (i.e., before the rehabilitation program starts) is planned. In Study Part 2, the use of Ambulatory Assessment allows for data collection in daily life that is aligned with the time the participants execute their individual aftercare health behavior. In addition, an advantage of mixed methods designs is that qualitative data help explain results of quantitative data. Therefore, interviews with participants may provide additional information about how psychological determinants interact with the individual aftercare health behavior.

Possible challenges include the recruitment of patients prior to the start of the rehabilitation programs to build an adequate control group. Patients will receive the study material via post and a promotion letter of the rehabilitation center is supposed to increase the recruitment rate prior to rehabilitation. Furthermore, long follow-up periods with many measurement occasions often result in high drop-out rates and sample attrition (53). For that reason, researchers will send out reminders to fill out all questionnaires. Regarding Study Part 2, participants may change the aftercare health behavior they chose and switch time and dates when they plan to execute their behavior.

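### Study Part 1 announces an untreated control period (t0–t1), but its effectiveness statement, power analysis and stated analyses do not carry that comparison through

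*Protocol article*

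**What the plan says.** **The control.** Background criticises earlier work because "a control group is an essential component for robustly evaluating the effectivity of the intervention which is missing in many studies". The Discussion answers that "a control period without treatment (i.e., before the rehabilitation program starts) is planned", and later in the same section calls this a control group. Section 2.1.1 (Sampling and participants) says that recruiting at t0 and again at t1 permits a "comparison of the indicators' development from the time without a rehabilitation program with the indicators' development after the rehabilitation program has started". Entry at t0 is optional, since patients can still join at t1, and no target number for t0 is given.

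**The timing.** The t0 questionnaire goes out "via post several weeks before the rehabilitation program starts". Section 2.1.2 says: "Typically, rehabilitation programs last three to four weeks". Follow-up from t2 to t8 is six-monthly over three years.

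**The analysis.** Section 2.1.3 (Data collection) says that t1 and t2 are measured to assess effectivity. The power analysis in 2.1.1 uses the eight occasions since programme start. Section 2.1.4 (Data analysis) states: "Initially, repeated measures analyses of variance will be utilized to assess changes in subjective health, work ability, BMI, and physical activity behavior over time". It adds that the method can evaluate "between-subjects effects (differences among groups"), without saying which groups, and that latent growth curves will describe trajectories over the study period.

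**The concern.** All participants receive rehabilitation as usual, so t0–t1 is the only untreated time in the study. It can serve as a control only if the change during it is set against the change during the programme. The three places that define how effectiveness is measured, powered and analysed do not do this: one uses t1 versus t2, one leaves t0 out, and one speaks only of change over time.

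A change from t1 to t2, or a time effect over t1–t8, contains whatever natural recovery and regression to the mean occur alongside treatment. Reading it as effectiveness would repeat the weakness that Background holds against earlier studies. For t3–t8 no untreated course exists at all, yet the aims speak of durable and long-term effects.

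**Working it through.** **1. The plan's own sample size.** Inputs from 2.1.1: f = 0.05, α = 0.05, power 0.80, r = 0.50, m = 8 occasions, repeated-measures ANOVA with within-between interaction. The number of groups k is not stated; k = 2 is back-solved.

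- λ = f²·N·m/(1−r) = 0.0025 × 360 × 8 / 0.5 = 14.4
- df1 = (k−1)(m−1) = 7; df2 = (N−k)(m−1) = 358 × 7 = 2,506
- Power = 0.8003, so n = 360 reproduces exactly.

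A one-group time effect over eight occasions also gives 360. With nine occasions (t0–t8) the same formula gives 335. The figure therefore rests on t1–t8. The recruitment target of 1,101 equals 360 × 1.15⁸ = 1,101.2.

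**2. What the unnamed groups could be.** If they were t0-recruits and t1-recruits, both would be treated from t1 onward. Their interaction with time over t1–t8 would still not compare treated with untreated time.

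**3. The announced contrast.** Let D = (t2−t1) − (t1−t0) = t2 − 2·t1 + t0. Assume compound symmetry with r = 0.50 and work in SD units:

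- Var(D) = 1 + 4 + 1 + 2 × 0.5 × (−2 − 2 + 1) = 3
- For comparison, Var(t2−t1) = 2(1 − 0.5) = 1

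Assume also no change in t0–t1 and a change of d in t1–t2, so that the expected D equals d. The test is a two-sided one-sample t-test at 0.05. The plan chose d = 0.10; 0.17 and 0.25 are the ends of the meta-analytic range it cites for cardiovascular rehabilitation.

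Cases remaining at t2 after two 15% losses (after t0 and after t1):
- all 1,101 enter at t0: 1,101 × 0.85² ≈ 795
- half enter at t0 (illustrative, as no share is given): 0.5 × 1,101 × 0.85² ≈ 397

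| d | n for D, 80% power | n for plain t1–t2, 80% power | power for D, 795 cases | power for D, 397 cases |
|---|---|---|---|---|
| 0.10 | 2,357 | 787 | 0.37 | 0.21 |
| 0.17 | 817 | 274 | 0.79 | 0.50 |
| 0.25 | 379 | 128 | 0.98 | 0.82 |

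At the plan's own effect size the contrast needs about three times as many complete cases as a plain pre-post test, and more than the whole recruitment target. These figures are for raw changes; scaling by elapsed time would alter them unless the two intervals are equal.

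**4. Interval length.** The wait is several weeks and the programme typically three to four. Nothing fixes the first, so the two may or may not match. Programme duration is listed as a control variable in 2.1.4; the length of the wait is not.

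**The case against.** The strongest reply is that the comparison is announced in 2.1.1 and again in the Discussion, that all instruments are given at t0, and that either a repeated-measures ANOVA or a growth curve including t0 could carry it. Planned contrasts and time scores are details that an article usually leaves to a fuller document. That stands: it would be wrong to say that the plan never contemplates the contrast, and the absence of model detail alone is no fault. It does not answer the mismatch between positive statements in the same article. Effectivity is tied to t1 and t2, and the sample size to occasions since programme start. A fuller analysis plan could name the contrast, but it would not change the basis of the stated power or give t3–t8 a comparator.

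Three stronger readings are tempting and not supported:

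- *The two intervals differ in length.* The wording shows only that t0–t1 is not fixed and may differ.
- *The bias from unequal intervals can be sized.* The document gives neither a natural drift rate nor a waiting time in weeks, so any figure would rest on invented inputs.
- *The study can yield only an uncontrolled pre-post result.* This does not describe the t0-recruits, whose data do permit a within-person control for the immediate effect. It applies to t1-recruits and to t3–t8.

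It is also fair to say that the missing long-term comparator is a limit of the design, which no analysis can remove. What can be corrected is how those results are described.

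**Conclusion.** The concern holds as a mismatch within the protocol. The control-period comparison promised in 2.1.1 and the Discussion is not carried into the effectiveness statement in 2.1.3, the power analysis in 2.1.1 or the analyses in 2.1.4. As stated, effectiveness is a pre-post change that cannot be separated from natural recovery or regression to the mean.

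The contrast that would help is weakly powered at the planned d = 0.10: about 0.37 at best and about 0.21 if half enter at t0. It is reasonably powered only nearer 0.25. These values depend on the assumptions of compound symmetry, r = 0.50, no change in t0–t1, two 15% losses and the assumed t0 share. Low power is a reason to state the precision openly, not a reason to fall back on the pre-post change. The contrast also assumes that the untreated course seen in t0–t1 would have continued through t1–t2.

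**What to change.** - In 2.1.4, name as the effectiveness contrast the change during t1–t2 minus the change during t0–t1, among people recruited at t0. Use a model that includes t0 and actual elapsed time, for example a piecewise mixed or growth model with knots at t1 and t2. People recruited at t1 inform only the later segments.
- Align the effectivity statement in 2.1.3 with this contrast.
- Record completion dates if they are not already captured; the article does not say whether they are.
- In 2.1.1, state that the n = 360 / 1,101 calculation does not cover this contrast, and give its expected precision for a plausible range of t0 entry.
- Report t3–t8 as maintenance or change from t2, not as an effect attributed to rehabilitation.
- In the Discussion, replace the term control group with pre-rehabilitation control period.

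No new measurement occasions are needed. The cost is wording, possibly a date field, lower precision because only t0-recruits inform the contrast, and a more modest long-term claim.
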